**Exploratory endpoints**	
TDM in blood	Association of MTX-PGs levels and CDAI response at week 12 and week 24
	Association of MTX dosage, MTX-PGs levels and TTV titre as a potential marker to guide levels of immunosuppressive therapy at week 12 and week 24
Sweat analysis	Association between treatment-associated biomarker profiles and longitudinal clinical outcomes
GC dose	Difference in cumulative GC dose between treatment arms
Treatment adherence	Association of CDAI response and treatment adherence as measured by paper-based questionnaires, MTX metabolites and electronic adherence monitoring (in patients using the RheumaBuddy mobile app)
Safety parameters	Differences in safety profile according to number of AEs and organ systems (haematologic, hepatic, gastrointestinal, infections)
Disease trajectory	Trajectories of disease activity in the two groups over all visits, and its relation to predictors

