### Criteria for discontinuing or modifying allocated intervention/comparator {15b}

Criteria for discontinuation or modification of the allocated intervention or comparator include safety concerns, serious or persistent adverse events, pregnancy, protocol deviations affecting participant safety, or investigator judgement. Participants may withdraw consent at any time without consequences for further treatment or study participation.

In case of a worsening of disease activity (CDAI increase > 4.5 compared to baseline) at each visit from week 4 onwards or inadequate improvement of the sum of swollen and tender joints (< 20% change compared to baseline) from week 12 onwards, rescue treatment applies according to standard of care (such as switch or add on of conventional synthetic, biologic or targeted synthetic DMARD (cs/b/tsDMARD)). This results in the participant’s early termination from the study. Non-responder imputation will apply to all patients with a premature end of study.

In case of an AE, a diagnostic or therapeutic procedure, an abnormal assessment (e.g. laboratory abnormalities) the MTX dose can be temporarily interrupted or reduced to ≥ 10 mg/week and re-escalated to 25 mg after resolution of the problem. If drug interruption or intermittent reduction is within a timeframe of ≤ 3 weeks, and re-institution of full dose of the study drug is safe according to the decision of the investigator, no permanent study discontinuation is required.

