### Concomitant care permitted or prohibited during the trial {15d}

All participants will receive an open-label short-term GC pulse at baseline according to standard of care for active RA on MTX. The prednisone-equivalent dose and a standardised tapering scheme will be prescribed by the investigator and initiated on day 1 after baseline. GC intake during the first 4 weeks will be recorded in a patient diary. GC use beyond the initial taper will be documented at each visit.

Folate supplementation will be prescribed as standard of care for MTX therapy according to a predefined scheme and recorded as concomitant medication.

Permitted concomitant medications.TNFα inhibitors (stable ≥ 4 months)csDMARDs (stable ≥ 4 months)NSAIDs and analgesics at investigator’s discretion

Prohibited concomitant medications.

Initiation or dose escalation of immunomodulatory therapies. Introduction of additional cs/b/tsDMARDs, or other immunosuppressants will lead to discontinuation of the investigational product.

Participants will be instructed not to initiate any new medication without prior consultation with the investigator.

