### Ancillary and post-trial care {34}

A voluntary follow-up visit occurs 4 weeks after premature discontinuation of the study drug, during which clinical disease activity and relevant laboratory safety and inflammatory parameters are assessed. After completion of the trial, participants return to routine standard-of-care follow-up.

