### Harms {17}

MTX is associated with a well-characterised adverse event profile, including gastrointestinal symptoms (nausea, vomiting, stomatitis), elevated liver enzymes, haematologic abnormalities (e.g. leukopenia) and rare pulmonary or infectious complications. In this study, all anticipated and unexpected adverse events (AEs) are recorded throughout participation. Expected harms include those commonly reported with MTX or GC therapy, while unexpected harms are any other events not described in product information or standard care. AEs are assessed systematically at each study visit and coded using standardised terminology (MedDRA). All AEs are captured in the study database, and summaries of clinically relevant harms will be reported in trial publications.

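### The safety endpoint is worded as a count of adverse events although treatment failure ends observation early, so unequal early termination can understate AEs in the arm with more failures

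*Protocol article*

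**What the plan says.** The exploratory part of Table 1 (Outcomes, item 16) words the safety endpoint as "Differences in safety profile according to number of AEs and organ systems" and the GC endpoint as "Difference in cumulative GC dose between treatment arms". Neither line gives a denominator, a rate or a common time window, and Table 1 lists no other between-arm safety comparison.

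Section 15b sets two triggers for rescue treatment: "worsening of disease activity (CDAI increase > 4.5 compared to baseline) at each visit from week 4 onwards", and "inadequate improvement of the sum of swollen and tender joints (< 20% change compared to baseline) from week 12 onwards". Either one leads to "early termination from the study".

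Data collection follows participation. The Harms section (item 17) states that "all anticipated and unexpected adverse events (AEs) are recorded throughout participation". Section 15d states that "GC use beyond the initial taper will be documented at each visit". After an early stop, section 34 offers little more: "A voluntary follow-up visit occurs 4 weeks after premature discontinuation of the study drug". That visit covers disease activity and laboratory parameters.

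Non-responder imputation (items 27b and 27c) deals with responder status and cannot repair a count or a summed dose. For time to remission, item 27b handles unequal follow-up by censoring. Nothing equivalent is stated for the two endpoints above.

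**The concern.** An AE count grows with the weeks a participant is observed. Here those weeks depend on outcome, because failing participants leave and most of their later AEs go unrecorded. The trial expects more remission with subcutaneous than with oral MTX (20% versus 5% in the sample size section). If that is right, the oral arm plausibly loses more participants to the rescue rule and has less observed time, so fewer AEs are counted there at the same weekly rate.

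This matters because better tolerability is part of the rationale: the Background cites about 30% fewer gastrointestinal AEs with the subcutaneous route. A count that shrinks in the arm with more failures would understate such a benefit.

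**Working it through.** **Figures in the plan.** The article gives no expected AE rate, GC total or early-termination rate by arm. Its only attrition figure is the 16% dropout allowance, and that arithmetic reproduces: 76 / (1 − 0.16) = 90.5, so 91 per arm and 182 in total. It does not say whether the 16% includes rescue terminations. The exit rates below are therefore assumptions.

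**AE count.** Let d be the proportion leaving at week 12, with everyone else observed for 24 weeks. Mean weeks on study = 24(1 − d) + 12d. With the same constant weekly AE rate in both arms, the ratio of counts equals the ratio of mean weeks.

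| Exits at week 12, oral vs s.c. | Mean weeks, oral | Mean weeks, s.c. | Oral/s.c. count ratio | s.c./oral count ratio |
|---|---|---|---|---|
| 20% vs 12% | 21.6 | 22.56 | 0.957 | 1.044 |
| 40% vs 25% | 19.2 | 21.0 | 0.914 | 1.094 |
| 30% vs 30% | 20.4 | 20.4 | 1.000 | 1.000 |

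The first row averages 16%, (20 + 12)/2, which matches the planning allowance. The second averages 32.5%, about twice that.

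If the true s.c./oral rate ratio were 0.70, the count ratio would be 0.70 × 1.044 = 0.73 in the first row and 0.70 × 1.094 = 0.77 in the second.

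**If AEs cluster early.** Suppose all AEs occurred before week 12 and did not differ by arm. The counts would then be equal, and events per patient-time would be too high in the arm with more exits. At 40% versus 25% the s.c./oral rate ratio would read 19.2/21.0 = 0.91 instead of 1.00.

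**GC dose.** Section 15a gives every participant a four-week course, which ends at zero for those not on GC at entry and at the entry dose (up to 10 mg daily) for the rest.

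- A non-user at entry who leaves at week 12 loses none of the scheduled course, so the cumulative dose is unaffected unless there is additional use later.
- A participant on 10 mg daily, the highest permitted entry dose, loses 10 × 84 days = 840 mg from the recorded total by leaving at week 12.
- For a whole arm, write the total as T + q × g × 7 × [20(1 − d) + 8d], where T is the course total, q the share on GC after week 4 and g their daily dose. Assume exits of 40% versus 20%, T of 280 to 560 mg, q of 30% to 50% and g of 5 to 10 mg. At T = 280, q = 0.5 and g = 10 this gives 812 versus 896 mg, ratio 0.91. At T = 560, q = 0.3 and g = 5 it gives 720 versus 745 mg, ratio 0.97. The recorded total in the arm with more exits is thus roughly 3% to 9% lower.

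**Averaging GC over all time on study.** For a non-user at entry, the mean daily dose is T/168 on completion but T/84 after a week-12 exit: the same intake, twice the value. With 40% versus 25% exits, the oral/s.c. ratio of means is (0.60 + 0.40 × 2)/(0.75 + 0.25 × 2) = 1.40/1.25 = 1.12, a spurious 12% excess.

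**The case against.** The strongest reply is that the article does not describe the analysis. Table 1 gives one-line labels, the methods section covers primary and secondary outcomes only, and whether AEs appear as events, participants or rates is commonly settled in an SAP, which is not shown. This stands in part: a reader might infer that unadjusted totals will be tested, and the article does not say so. What it does state is the measure, a number of AEs, and that measure depends on observation time in a trial whose rules shorten observation after failure.

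The second reply is that the direction and size are conditional. This stands in full. The distortion needs unequal exits. Participants who fail may also have a different weekly AE rate before leaving, and early clustering of AEs would shrink the effect.

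The third reply concerns GC. A reader might infer that entry users make up most of the cumulative dose and that the total mainly reflects length of stay. The article gives no share of GC users at entry, everyone receives the initial course, and randomisation balances entry use in expectation. That stronger reading is not supported.

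**Conclusion.** The point holds as a minor one. The stated safety measure can understate AEs in whichever arm has more early terminations: by about 4% at 20% versus 12% exits, about 9% at 40% versus 25%, and not at all at equal exits. These figures assume exits at week 12 and a constant AE rate common to both arms; the article supplies neither.

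A reader might infer that the arm with more failures will end up looking safer. The numbers do not support that as a general statement: a true rate ratio of 0.70 in favour of the subcutaneous arm would still show as 0.73 to 0.77. The expected effect is a mild attenuation, or a small spurious difference when the true rates are equal.

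Cumulative GC dose is affected more narrowly, only through use after week 4. Both endpoints are exploratory, and the primary endpoint and the test hierarchy are untouched.

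**What to change.** Amend two lines of Table 1, or state the same in the SAP:

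- **Safety:** AEs per patient-time on study by organ system, as a rate ratio with 95% CI that allows for repeated events in one participant, alongside the proportion of participants with at least one AE. Report time on study and early termination by arm.
- **GC:** keep the cumulative dose. Add GC dose after week 4 per day observed, adjusted for daily dose at entry, and state how many participants left too early to contribute. Do not average the common four-week course over total time on study.

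The cost is small. AEs and GC use are already recorded at dated visits, so no new data are needed. The downside is that a single rate assumes a roughly constant hazard. Early clustering should be checked, for example by showing AE rates before and after week 12 separately.

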### Exploratory laboratory assessments

MTX-PGs, MTX in plasma and the 7-OH-MTX are assessed at baseline, weeks 4, 12 and 24. One EDTA blood sample tube is taken, inverted 5 times and put immediately on crushed ice for exactly 30 min before centrifugation for 15 min at 4 °C and 2.000 × g. From this sample, the plasma and RBC pellet aliquots are stored at − 80 °C and regularly shipped on dried ice to the Medical University of Vienna for analysis. The MTX-PG 2–7 are analysed from the RBC pellet aliquots with a liquid chromatography-electrospray ionisation-tandem mass spectrometry-based assay using stable-isotope-labelled internal standards. The concentrations of MTX-PGs are reported in nmol/L packed erythrocytes.

One plasma aliquot collected at baseline, weeks 4, 12 and 24 is used for extraction of the viral DNA for the TTV analysis, using polymerase chain reaction at the Leiden University Medical Centre.

The sweat samples are obtained non-invasively from finger sweat using filter paper. The patients are instructed on sweat sampling method at the baseline visit, perform the first sampling under the supervision of study personnel, and the subsequent samples at home according to a diary. The samples are analysed at the Department of Analytical Chemistry at the University of Vienna.

### Adherence assessments

To assess treatment adherence, the RheumaBuddy application, a paper-based questionnaire (BAASIS-MTX), and the measurement of biomarkers are used.

Patients are introduced to RheumaBuddy, an existing Health App (www.rheumabuddy.com) and may choose to use it in accordance with its terms and conditions. Consenting patients are registered during baseline visit by using a study and centre specific code. In the MethMax-adapted version of the application, patients will receive weekly reminder to fill in information on painful joints on a homunculus, disease related symptoms on a numeric rating scale, and last MTX intake. Optionally, patients can report symptoms more frequently, in a need-adapted manner.

At each study visit, a paper-based questionnaire is used to assess adherence. For this purpose, a validated BAASIS© questionnaire for transplanted patients on immunosuppressive therapy (https://baasis.nursing.unibas.ch/) was adapted for the MethMax trial = BAASIS-MTX.

### Harms {17}

MTX is associated with a well-characterised adverse event profile, including gastrointestinal symptoms (nausea, vomiting, stomatitis), elevated liver enzymes, haematologic abnormalities (e.g. leukopenia) and rare pulmonary or infectious complications. In this study, all anticipated and unexpected adverse events (AEs) are recorded throughout participation. Expected harms include those commonly reported with MTX or GC therapy, while unexpected harms are any other events not described in product information or standard care. AEs are assessed systematically at each study visit and coded using standardised terminology (MedDRA). All AEs are captured in the study database, and summaries of clinically relevant harms will be reported in trial publications.

### Participant timeline {18}

The study flow chart is outlined in Fig. 1 and the study related assessments in Table 2 (SPIRIT figure). After the screening and baseline visits, patients undergo scheduled study visits at weeks 4, 12, 16 and 24 (± 7 days). At each visit, a blinded joint assessment, patient reported outcomes as well as inflammatory and safety laboratory parameters are performed. Patients are asked to complete three questionnaires: Health Assessment Questionnaire Disability Index (HAQ-DI), the 36-Item Short Form Survey (SF-36) and Functional Assessment of Chronic Illness Therapy (FACIT-Fatigue) to assess the patient-reported outcomes of disease activity and quality of life three times during the study period. At predefined timepoints, drug monitoring is conducted using measurements of MTX-metabolites and TTV in blood. The medication adherence is assessed via an electronic and paper-based adherence assessments and exploratory laboratory measurements. In total, patients undergoing all scheduled study visits remain in the trial for 24 weeks, when primary endpoint is assessed.

**Fig. 1 Fig1:**
[figure not shown]
Study flow chart, providing overview of the main inclusion/exclusion criteria, study assignment, efficacy assessments and main outcomes

**Table 2 Tab2:** Visit and assessment schedule (SPIRIT figure) according to the protocol version 2.0. Detailed description of laboratory parameters is found in section Data collection

Allowed visit window ± 7 days	**Screening (week-2)**	Baseline visit week 0	Visit week 4	**Visit week 12**	Visit week 16	**Visit week 24**
Written Informed Consent	**x**					
Demography and medical history	**x**					
Record RA classification criteria	**x**					
Inclusion/Exclusion Criteria	**x**	**x**				
Randomisation		**x**				
Distribution of study drug		**x**	**x**	**x**	**x**	
Concomitant Medications	**x**	**x**	**x**	**x**	**x**	**x**
Optional informed consent for electronic adherence (RheumaBuddy App)	**x**					
**Efficacy Assessments**						
Swollen joint count [31]	**x**	**x**	**x**	**x**	**x**	**x**
Tender joint count [31]	**x**	**x**	**x**	**x**	**x**	**x**
Evaluator global assessment (EGA)	**x**	**x**	**x**	**x**	**x**	**x**
Patient global assessment (PGA)	**x**	**x**	**x**	**x**	**x**	**x**
Patient pain assessment (on NRS)	**x**	**x**	**x**	**x**	**x**	**x**
Morning Stiffness (duration and on NRS)	**x**	**x**	**x**	**x**	**x**	**x**
Fatigue (on NRS)	**x**	**x**	**x**	**x**	**x**	**x**
Efficacy assessment CDAI change*			**x**	**x**	**x**	**x**
Efficacy assessment joint count change 20%*				**x**	**x**	**x**
FACIT-Fatigue Questionnaire		**x**		**x**		**x**
Quality of Life Questionnaire SF-36.v1		**x**		**x**		**x**
Disability Scale Questionnaire HAQ-DI		**x**		**x**		**x**
Adherence questionnaire BAASIS-MTX-visit specific		**x**	**x**	**x**	**x**	**x**
RheumaBuddy App use weekly (consent needed)		**x**	**x**	**x**	**x**	**x**
Patient diary MTX and folic acid weekly		**x**	**x**	**x**	**x**	**x**
Patient diary glucocorticoids daily		**x**	**x**	**(x)**	**(x)**	**(x)**
**Safety Assessments**						
Physical Examination	**x**	**x**				**x**
Symptom oriented physical exam		**x**	**x**	**x**	**x**	**x**
Vital Signs (blood pressure, pulse, temperature)	**x**	**x**		**x**		**x**
Symptom-directed exam	**x**	**x**	**x**	**x**	**x**	**x**
Adverse Events		**x**	**x**	**x**	**x**	**x**
**Laboratory Assessments**						
Haematology^1^	**x**^^^	**x**	**x**	**x**	**x**	**x**
Serum Chemistry^2^	**x**^^^	**x**	**x**	**x**	**x**	**x**
CRP & ESR	**x**^^^	**x**	**x**	**x**	**x**	**x**
Pregnancy Test^3^	**x**	**x**	**x**	**x**	**x**	**x**
Hepatitis B and C testing^4^	**x**					
RF and anti-CCP^4^	**x**					
MTX-Polyglutamate sampling		**x**	**x**	**x**		**x**
Torque teno virus sampling		**x**	**x**	**x**		**x**
Biobank and PBMC collection optional		**x**	**x**	**x**		**x**
Sweat analysis sampling incl. diary		**x**		**x**		**x**

^*^In case of a disease flare, patient will be transferred to standard of care and an optional safety follow-up visit after 4 weeks will be scheduled

^1^Red blood cell count (RBC), haemoglobin (Hb), haematocrit (Hct), white blood cell count (WBC), platelet count (PLT)

^2^Creatinine (Crea), blood urea nitrogen (BUN), estimated glomerular filtration rate (eGFR), alanine aminotransferase (AST), aspartate aminotransferase (ALT), gamma-glutamyl transferase (GGT), alkaline phosphatase (AP), total bilirubin, albumin

^^^Window for blood assessment −7 days to 0

^3^Blood or urine; in women of childbearing potential at each study visit at the centre and self-reported test in weeks 8 and 20

^4^Within 6 months prior to screening

### Sample size {19}

Based on literature, the primary endpoint (CDAI ≤ 2.8, i.e. remission) is expected to be achieved by 5% of patients included in the p.o. dose arm, and by 20% in the s.c. arm of the trial [14, 32, 33]. Patients will be randomised in a 1:1 ratio, resulting in an expected sample size for the main outcome of 76 per group (based on *χ*^2^ statistics) with 80% power and a two-sided alpha of 0.05. To account for a conservative 16% dropout rate, the study aims to include 182 patients in total.

### Recruitment {20}

Potential participants with a documented diagnosis of RA who attend routine medical appointments at the co-sponsor sites are pre-screened by study personnel and approached for participation during a regular clinic visit. Potential participants may also be identified through referrals to the study centres. In Vienna, the referral platform Preferrix is used.

## Assignment of interventions: randomisation

### Sequence generation: who will generate the sequence {21a}

The random allocation sequence is generated by unblinded personnel using RANDOMIZER software (Institute for Medical Informatics, Statistics and Documentation, Medical University of Graz, Austria).

### Sequence generation: type of randomisation {21b}

Patients are randomised in a 1:1 ratio, using stratified randomisation by study centre. Details of the software’s randomisation algorithm and any blocking to reduce predictability are documented internally and are not accessible to personnel enrolling participants or assigning interventions.

### Allocation concealment mechanism {22}

Allocation is implemented centrally via the RANDOMIZER software with personalised user accounts for unblinded personnel. The sequence is concealed from joint assessors, who remain blinded to the study assignment throughout the trial.

### Implementation {23}

Personnel enrolling participants do not have access to the random allocation sequence. Randomisation is performed by unblinded personnel with personalised accounts, while the joint assessors who perform outcome measurements remain blinded.

## Assignment of interventions: blinding

### Who will be blinded {24a}

Joint assessors performing outcome measurements are blinded to participants’ study assignments. Patients, care providers and personnel performing randomisation are not blinded.

### How will blinding be achieved {24b}

Blinding is maintained by ensuring that joint assessors do not have access to the random allocation sequence in the RANDOMIZER software and do not communicate with unblinded study personnel or participants about any study-related details. Joint assessors also do not have access to patient data or electronic case report forms.

### Procedure for unblinding if needed {24c}

No emergency unblinding procedures are required, as the trial design does not involve blinded treatment administration. In the unlikely event that unblinding is necessary for safety or clinical reasons, it will be performed by the unblinded study personnel responsible for randomisation and documented in the study records.

## Data collection and management

### Plans for assessment and collection of outcomes {25a}

The following data is collected: demography (age, sex, height, weight, body mass index, ethnic origin, and childbearing potential), medical history (RA, relevant comorbidities), medication history (MTX, folic acid, GC, NSAID and other concomitant medication), disease activity of RA (pain, stiffness, patient global assessment, evaluator global assessment, tender joints, swollen joints, CDAI) and physical examination. The quality of life and subjective disease assessments are performed using questionnaires: HAQ-DI, SF-36 and FACIT-Fatigue. The treatment adherence is assessed with the Basel Assessment of Adherence to Immunosuppressive Medication Scale (BAASIS)-MTX questionnaire, entries within the mobile application RheumaBuddy and the measurement of biomarkers. Haematologic laboratory parameters include red blood cell count (RBC), haemoglobin (Hb), haematocrit (Hct), white blood cell count (WBC), platelet count (PLT). The serum chemistry includes creatinine (Crea), blood urea nitrogen (BUN), estimated glomerular filtration rate (eGFR), creatine kinase (CK), lactate dehydrogenase (LDH), alanine aminotransferase (ALT), aspartate aminotransferase (AST), gamma-glutamyl transferase (GGT), alkaline phosphatase (AP), total bilirubin and albumin. Tests for hepatitis B and C, as well as the rheumatoid factor and anti-CCP antibodies, are performed at screening, unless there is an available result less than 6 months old. Pregnancy test is performed in women of childbearing potential at each study visit at the centre as either urinary or blood test, except for a urinary test at home at weeks 8 and 20, which is self-reported in a diary. Vital signs are assessed regularly.

Exploratory laboratory assessments include the plasma metabolites MTX and 7-hydroxymethotrexate (7-OHMTX), the intracellular MTX-PGs, TTV in plasma, as well as finger sweat.

